### Neuroimaging acquisition

MRI scans are collected on a 3.0 Tesla Siemens Prisma magnet system (Siemens Healthineers, Erlangen, Germany) utilising a 64-channel phased-array head/neck coil and VE11C software. Specialised equipment from Thulborn Associates (Chicago, IL) and Lumina (Cambridge Research Systems, Kent, UK) is used to facilitate the fMRI data collection.

#### Resting-state fMRI

A resting-state echo-planar imaging (EPI) gradient echo (GRE) sequence is acquired with the following parameters: repetition time (TR) =1500 ms, echo time (TE) =33 ms, field of view (FOV) =255 mm, matrix = 104 × 104, flip angle = 85°, acceleration factor (IPAT) = 6, phase-encoding direction = anterior to posterior. Sixty contiguous axial/oblique slices with a slice thickness of 2.5 mm are acquired to cover the whole brain. Eight dummy scans are acquired at the start of every acquisition to allow magnetization to stabilize to steady state. A total of 320 measurements are subsequently acquired during the Resting State period, resulting in a total scan time of 8 minutes and 12 s.

#### Structural T1 MPRage

A high-resolution isotropic 3-dimensional (3D) T1-weighted volume dataset is subsequently acquired in the sagittal plane using an inversion recovery (IR)-prepared spoiled gradient echo (MP-RAGE) sequence with the following parameters; TR = 2400 ms; TE = 2.21 ms; time following inversion pulse (TI) = 900 ms; FOV = 256 mm; matrix = 288 × 288; flip angle = 8°; multi-slide mode = single shot; IPAT = 2; phase-encoding direction = A/P. A total of 192 slice locations are acquired with an effective slice thickness of 0.9 mm covering the whole brain in a scan time of 6 minutes and 23 s. This 3D dataset is collected for use in a unified segmentation approach for normalization of the fMRI data to standard space.

#### Task-based fMRI

PsychoPy software (version 1.85.3) is used for the delivery of functional stimulus. Two functional tasks are performed during image acquisition utilising a GRE EPI sequence with the following parameters: TR = 3000 ms, TE = 20 ms, FOV = 240 mm, matrix = 104 × 104, flip angle = 90°, IPAT = 2, phase-encoding direction = A/P. During each task, 55 contiguous axial/oblique slices with a slice thickness of 2.5 mm are acquired to cover the whole brain. For the Pavlovian-Instrumental Transfer (PIT) task, 284 measurements are acquired during the task period, resulting in a total scan time of 14 minutes and 27 s. For the Devaluation task, 120 measurements are acquired during the task period, resulting in a total scan time of 6 minutes and 15 s.

#### Diffusion weighted imaging

A multi-shell EPI DTI technique with 3 separate acquisitions of 64 axial slices each is also utilized with the following parameters: TR =3500 ms: TE = 71 ms: matrix = 110 × 110: FOV = 260 mm: slice thickness = 2.4 mm; IPAT = 2: phase-encoding direction = A/P. Acquisition 1 (4 mins 23 s) is 69 directions with b-values of 0 and 2800 s/mm^2^; acquisition 2 (3 mins 16 s) is 50 directions with b-values of 0 and 2000 s/mm^2^; acquisition 3 (2 mins 6 s) is 30 directions with b-values of 0 and 1000 s/mm^2^. A pair of gradient reversal sequences (AP and PA k-space trajectories) are also acquired for distortion correction.

## Measures

### Clinical measures

#### Number of binge eating days per week

The number of binge eating days will be recorded pre- and post- treatment as a measure of BED symptom improvement.

#### Clinical global impressions – Severity [30]

The CGI-S score will also be recorded pre- and post- treatment as a measure of BED symptom improvement.

### Neuroimaging measures

#### Resting-state functional magnetic resonance imaging (rs-fMRI)

During the resting-state scan, participants are asked to “keep your eyes open and try to keep them on the cross. Try to remain still but not fall asleep”. A key measure extracted from this data will be connectivity strength, which is derived from the degree of synchronisation of very low frequency neuronal oscillations between each node across time. Descriptive features of the neuronal networks derived from graph-theory will also be produced, such as small-worldness, modularity and network efficiency [25].

#### Task-based functional magnetic resonance imaging (fMRI) – Pavlovian-instrumental transfer and devaluation Tests [33]

Outside of the scanner, participants learn to use specific actions to liberate snack foods from a vending machine. They also learn about the reward value of the foods, changes in reward value, and the relationship between various predictive stimuli and food delivery. Within the scanner, the PIT Test aims to evaluate the ability of subjects to use experienced or predicted value to guide goal-directed actions. Subsequently, the reward value of the food is manipulated via disgust (a video of cockroaches on the food). The Devaluation test is used to assess the ability of subjects to adjust their food-seeking actions based on changes in current reward value.

#### Diffusion weighted imaging

This scan of white matter structure allows for analysis of the structural architecture of the brain and the integrity of white matter pathways. Measures of white matter integrity, produced using tract-based spatial statistics, will include fractional anisotropy (FA) and mean diffusivity (MD). Probabilistic tractography will be conducted to examine the white matter connectome and assess connectivity strength between specific nodes.

### Symptom-related measures

Self-report and interview-based questionnaires detailed below will be administered at both baseline and week 8 for BED participants, and at baseline only for control participants.

### Eating-related behaviours and cognition

#### Self-report measures

The Three-Factor Eating Questionnaire [34] assesses 3 cognitive and behavioural aspects of eating: dietary restraint, disinhibition and hunger. The Binge Eating Scale [35] measures the behavioural, emotional and cognitive symptoms associated with binge eating. The Eating Disorders Examination Questionnaire [36] measures eating disorder psychopathology in the past month related to restraint, eating concern, shape concern, and weight concern, as well as behavioural symptoms related to these concerns. The Loss of Control Over Eating Scale [37] is a measure of multiple aspects of loss of control whilst eating.

#### Researcher-administered measures

The Yale-Brown Obsessive Compulsive Scale Modified for Binge-Eating is a modified form of the Yale-Brown Obsessive Compulsive Scale [38] that has been used in prior randomised controlled trials of LDX in BED [17–19] and measures the obsessiveness of binge eating thoughts and compulsiveness of binge eating behaviours.

### Impulsivity

The Barratt Impulsiveness Scale [39] is a self-reported questionnaire which measures personality and behavioural aspects of impulsivity in individuals.

### Other psychological symptoms

The Adult attention-deficit hyperactivity disorder (ADHD) Self-Report Scale [40] assesses the frequency of recent symptoms of ADHD in adults. The researcher-administered Hamilton Rating Scale for Depression [32] and Hamilton Anxiety Rating Scale [41] assess the severity of depression and anxiety symptoms, respectively.

### Quality of life

The self-reported WHO Quality of Life-BREF is a shortened form of the WHO Quality of Life-100 assessment [42] and is commonly used in epidemiological studies and clinical trials. It measures four broad domains related to quality of life: physical health, psychological health, social relationships, and the environment.

### Laboratory-based cognition

With the exception of the WTAR (baseline only), the tasks detailed below will be administered at both baseline and week 8 for all participants.*Wechsler Test of Adult Reading* (WTAR) [43]. A short word reading task that provides a measure of premorbid intelligence.*GoNoGo* [44]. In this task, the colour of the word ‘PRESS’ is frequently presented in green (Go) and infrequently in red (No Go). The participant is required to inhibit circle-tapping responses on red. This task measures target detection rate, response time, errors of commission and omission. The GoNoGo is a test of behavioural inhibition.*Stroop test* [45]. There are two sections to this test. In the first, the participant is required to indicate the colour that the written word spells (and not the incongruent ink colour that the word is written in). In the second section, the subject is asked to name the ‘ink’ colour a word is written in (and not read the actual word). The ‘interference’ experienced from the written word is called the ‘Stroop’ effect. The interference arises from the fact that reading is a highly over-learned skill and occurs automatically unless there is a sustained attentional focus to suppress the reading response. This assesses selective attention capacity and cognitive processing speed.*Monetary Incentive Delay (MID) Task* [46]. The MID task requires an individual to react to a target stimulus presented after an incentive cue to win or to avoid losing the indicated reward. In doing so, this paradigm allows the detailed examination of different stages of reward processing like reward prediction, anticipation, outcome processing, and consumption.*Value-modulated attentional capture* [47]. In this visual search task, certain stimuli signal the magnitude of available reward, but reward delivery is not contingent on responding to those stimuli. Indeed, any attentional capture by these critical distractor stimuli leads to a reduction in the reward obtained. Attentional capture is measured using eye-tracker equipment. Any counterproductive capture by task-irrelevant stimuli is important because it demonstrates how external reward structures can produce patterns of behavior that conflict with task demands, and similar processes may underlie problematic behavior directed toward real-world rewards. This measures reward sensitivity in involuntary attentional capture.

### Genetic analysis

BED participants will be given the option to provide a sample of their saliva for genetic analysis. Separate informed consent is obtained for participants who opt-in. The sample will be used to extract DNA and investigate single-nucleotide polymorphisms (e.g. DRD4, DRD5) relating to the pharmacogenetics of LDX.

### Primary outcomes

Resting-state intrinsic connectivity metrics and the number of binge eating episodes, pre- and post- LDX treatment, are the primary outcome measures of this study.

### Secondary outcomes

LDX treatment effects on activation and connectivity evoked during the PIT and Devaluation Tests, and behavioural performance on these tasks, are key secondary outcomes. Analyses will also be undertaken to examine LDX treatment effects on all symptom-related measures, and cognitive tasks outlined above. Potential side-effects (e.g. change in BMI) will be examined as covariates in analyses of treatment effects.

### Supplementary outcomes

Comparisons will be made between the pre-treatment BED group and healthy controls on the full range of measures to better characterise symptoms, cognition and neural function in BED.

### Sample size calculation

Forty individuals with BED will be recruited for this study. At the Brain Dynamics Centre, we have a record of high treatment trial retention rates (e.g. Methylphenidate trial in child and adolescent ADHD, 98%) and minimal neuroimaging data being discarded due to excessive motion (e.g. in young adults with depression, 2–3 individuals/ 40 recruited). Based on this history, we assume there will be a final sample size of approximately 35 for the primary outcome measures. This far exceeds previous imaging studies in BED (range of 11–22 participants per study) [7, 12, 13]. In addition, the pre- post treatment design enhances power due to the use of *within subjects* rather than *between groups* comparisons. A sample size of 35 should provide approximately 80% power to observe a medium effect size of 0.5 for a two-sided statistical analysis at an alpha value of 0.05. Studies examining fMRI connectivity changes between methylphenidate (a related stimulant) and placebo have observed strong effects with sample sizes much lower than that proposed here (e.g. *n* = 12) [48–50].

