## Method

### Participants

Approximately 40 participants with BED and 22 healthy matched controls will be recruited into the study. Both BED and control participants must be between 18 to 40 years of age (inclusive), and have a BMI between 20 to 45 kg/m^2^ (inclusive). BED participants are required to have a diagnosis of moderate to severe BED. This is based on Module I of the *Structural Clinical Interview for DSM-5 Research Version* (SCID-5-RV) [29]. Consistent with LDX efficacy studies [18, 19], moderate to severe BED severity requires a minimum of three days of binge eating per week in the past month and a minimum score of 4 on the *Clinical Global Impression – Severity* scale (CGI-S) [30], a clinician-determined summary measure of a patient’s global functioning. The *MINI International Neuropsychiatric Interview Version 7.0.2 for DSM-5* [31] (MINI) is also used to assess comorbid psychiatric disorders to determine eligibility and better characterise the cohort. The full inclusion and exclusion criteria for BED and control participants are listed in Tables 1 and 2.

**Table 1 Tab1:** Inclusion and exclusion criteria for BED participants

Criteria	List
Inclusion	• Age 18–40 years.
	• BED diagnosis, confirmed by the eating disorders module of the Structured Clinical Interview for DSM-5.
	• Moderate to severe BED, defined as the presence of binge eating frequency of ≥3 days/week in the month prior to the baseline assessment and a score of ≥4 on the clinical global impressions severity scale.
	• BMI of 20 – 45 kg/m^2^.
	• A study doctor has verified that it is medically and psychiatrically safe for their patient to commence LDX.
	• Fluent in English.
	• Have provided written informed consent.
Exclusion	• History of psychosis or mania.
	• Pregnant or breast-feeding women.
	• Current therapy with antipsychotics or noradrenaline reuptake inhibitors.
	• Current therapeutic intervention specific to treating eating behaviours and/or cognitions.
	• Cardiovascular disease, hypertension, use of monoamine oxidase inhibitors, or any other contraindications for psychostimulants.
	• History of substance abuse/dependence (excluding nicotine).
	• Previous suicide attempts or current suicidal ideation.
	• Known medical condition, disease or neurological disorder which might, in the opinion of investigator/s, interfere with the assessments to be made in the study or put BED patients at increased risk when exposed to optimal doses of the drug treatment.

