### Data analysis

Only the data from individuals with a medication compliance rate of ≥60% will be included in primary outcome analyses. For all analyses, a *p* value of < 0.05 will be considered statistically significant and relevant corrections for multiple comparisons will be applied.

Framewise displacement—movement of the head from one volume/timepoint to the next—and scaled signal intensity differences between contiguous volumes, will be calculated for each rs-fMRI time series during the quality control process. Temporal masks will be applied to censor volumes including motion, and participant data will be excluded from analyses if more than 1/3 of the time course data requires temporal masking.

Functional connectomics involves the study of brain connectivity, first by identifying the nodes (distinct brain regions) and subsequently estimating the functional connections (network edges) between these nodes [51]. Both voxel-wise and brain atlas parcellation approaches (e.g. Gordon parcellations) [52] will be utilised to designate nodes. Data-driven, whole-brain analyses using methods such as multivariate distance matrix regression [53] and network based statistics [54] will then be applied to rs-fMRI data to characterise pharmacological effects across the functional connectome, and assess correlations with symptom measure changes. Using a similar approach to Yang et al. [55], the results of data-driven analyses will be followed up using seed-based functional connectivity analyses. Connectomic measures will be computed for BED participants at baseline and post-treatment. A paired-sample t-test will be performed to compare baseline and post-treatment connectivity profiles to confirm the treatment effect. To examine any normalisation effects of LDX in BED participants, two independent sample t-tests will be conducted to compare functional connectivity between healthy controls, and the BED group at baseline and post-treatment, respectively. To examine the association of changes in functional connectivity and clinical improvement, we will correlate change scores (Δ = BED post-treatment – BED baseline) of functional connectivity with changes in the number of binge-eating episodes.

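### The stated 80% power holds for one uncorrected paired test; it does not describe the corrected connectome-wide primary analysis, and the two hypothesis tests have no power figure

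*Protocol article*

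**What the plan says.** The Sample size calculation section plans recruitment as "Forty individuals with BED will be recruited for this study". After losses, "we assume there will be a final sample size of approximately 35 for the primary outcome measures". It argues that "the pre- post treatment design enhances power due to the use of" within-subject instead of between-group comparisons, and then states: "A sample size of 35 should provide approximately 80% power to observe a medium effect size of 0.5 for a two-sided statistical analysis", with alpha set at 0.05. It does not name the test, the outcome, the scale of the 0.5, or any correction.

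The Primary outcomes section names two kinds of outcome, both measured before and after treatment: resting-state connectivity metrics (in the plural) and the number of binge eating episodes.

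The Data analysis section says of all analyses that "relevant corrections for multiple comparisons will be applied". It plans data-driven whole-brain analyses, with nodes defined both by voxel and by atlas parcellation, using methods such as multivariate distance matrix regression and network based statistics. It then plans:

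- a paired t-test of connectivity, baseline against post-treatment, in the BED group;
- two independent-sample t-tests against healthy controls, at baseline and post-treatment, to examine normalisation;
- a correlation of change scores "of functional connectivity with changes in the number of binge-eating episodes".

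On numbers, the Participants section says: "Approximately 40 participants with BED and 22 healthy matched controls will be recruited into the study". The Abstract and the Background give the hypotheses: that treatment normalises connectivity in reward and impulse-control circuits, and that this goes with less binge eating.

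**The concern.** The power paragraph uses an uncorrected 0.05, while the analysis section says corrections apply throughout. The paragraph also introduces its sample of 35 as the one for the primary outcome measures, and connectivity is one of these. A reader would therefore take the connectivity analysis to have about 80% power for a medium effect. The figure is not a property of that analysis.

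The paragraph is also silent on the two analyses that carry the hypotheses. Normalisation is examined between groups, against 22 controls, so the within-subject gain in power does not apply to it. The link with symptoms is examined by a correlation in about 35 people.

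The control comparison matters most. If BED participants differ from controls at baseline but not significantly after treatment, that pattern invites the conclusion that connectivity has normalised. With low power, it can also arise because a remaining difference was missed. Here low power could lead to a wrong positive conclusion as well as a missed effect.

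**Working it through.** **Inputs.** From Sample size calculation: n = 35 BED participants analysed, effect 0.5, two-sided alpha 0.05. From Participants: 22 controls. The article does not give the number of tests, the form of correction, or an expected correlation.

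**1. Reproducing the stated figure.** Paired t-test, with 0.5 read as mean change divided by the SD of the changes:

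- df = 35 − 1 = 34; critical t = 2.032
- noncentrality = 0.5 × √35 = 2.958
- power from the noncentral t = 82.0%

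The smallest n that reaches 80% is 34. The stated figure therefore reproduces as one paired test on one scalar outcome with no correction.

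**2. Effect of a stricter alpha on that same test.** The two lower alphas below are assumptions, used only to show a range; neither is in the article.

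| Two-sided alpha | Critical t (df 34) | Power at 0.5 | Change detectable with 80% power |
|---|---|---|---|
| 0.05 (stated) | 2.032 | 82.0% | – |
| 0.025 (0.05/2) | 2.345 | 72.8% | 0.54 |
| 0.005 (0.05/10) | 3.002 | 49.2% | 0.65 |

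These rows are for a single metric. They are not the power of network based statistics or distance matrix regression, which do not correct by dividing alpha among single tests. The power of those methods depends on how the effect is spread over the network, on which the article gives nothing.

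**3. BED versus controls.** Independent-sample t-test, 35 v 22, uncorrected alpha 0.05:

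- df = 35 + 22 − 2 = 55; critical t = 2.004
- noncentrality = 0.5 × √(35 × 22 / 57) = 0.5 × 3.675 = 1.838
- power = 43.9%
- d needed for 80% power = 0.78

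Even with no loss of BED participants (40 v 22), power would be 45.8%. For precision, the half-width of the 95% confidence interval for the difference at 35 v 22 is 2.004 × √(1/35 + 1/22) = 0.55 SD. An observed difference of zero would thus be compatible with a true difference of up to about half a standard deviation either way.

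**4. Change correlation.** Fisher z, n = 35, uncorrected alpha 0.05:

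- z needed for 80% power = (1.960 + 0.842) / √(35 − 3) = 2.802 / 5.657 = 0.495
- r = tanh(0.495) = 0.46

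Power by assumed r: 42% at 0.3, 67% at 0.4, 78% at 0.45, 87% at 0.5. Simulation gave 42% at 0.3, 80% at 0.45 and 88% at 0.5, in agreement.

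**The case against.** The strongest reply is that nothing in the power paragraph is false. The number reproduces. The sentence before it argues from within-subject comparisons, the primary outcomes are defined as pre-post measures, and a paired t-test of connectivity is planned. The article never claims 80% power for the control comparisons or for the correlation, and it lists pre-treatment comparisons with controls under supplementary outcomes. A condensed article may also leave power for further analyses to a fuller document.

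Much of this stands. There is no arithmetic error, and the figure fits one uncorrected pre-post test of binge episodes. Four stronger readings are tempting but unsupported:

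- **That most of the primary analyses are shown to be underpowered.** The article does not list the control tests and the correlation as primary analyses. What can be said is that its hypotheses rest on them and that no power is given.
- **That the corrected connectome tests have a particular low power.** The number of tests is not stated and the named methods are not Bonferroni tests, so no single figure can be given.
- **That the correlation has about 40% power.** This assumes r = 0.3, which is not in the article. The detectable r of 0.46 needs no such assumption.
- **That the 0.5 may be in raw SD units, which would make 80% depend on an unstated test-retest correlation.** Nothing in the text suggests this, and the standardised-change reading reproduces the figure.

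What the reply does not meet is the conflict within the article: power at an uncorrected 0.05 in one section, corrections for all analyses in the next. A separate analysis plan would not change what this paragraph tells its reader. The absence of power figures for the two hypothesis tests is a lesser matter, but the low power at 35 v 22 bears directly on how normalisation can be judged.

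**Conclusion.** The concern holds as a fault of scope. About 80% (82.0%) is correct for one two-sided paired t-test on one scalar outcome at uncorrected alpha 0.05, with a standardised mean change of 0.5. It is not the power of the primary connectivity analysis as planned, and that power cannot be derived from the article. The illustrative 73% and 49% show only the direction and rough size of the loss for one metric under assumed alphas.

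The two hypothesis tests have no stated power. Before correction, the control comparison at 35 v 22 has about 44% power for d = 0.5 and detects d = 0.78 with 80% power; the change correlation detects r of about 0.46. These figures assume 35 analysable BED participants, all 22 controls analysed, and roughly normal data. Multiplicity correction would make both less favourable.

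This is worth correcting but is not critical: no sample size or conduct has to change, and the stated number is right for the test that it describes.

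**What to change.** Reword the Sample size calculation paragraph in three respects:

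1. State that about 80% power applies to one paired pre-post comparison at uncorrected two-sided alpha 0.05, for a standardised mean change of 0.5, and not to the connectome-wide tests after correction.
2. Add the effects detectable with 80% power for the other two analyses, both before correction: d = 0.78 for BED versus controls (35 v 22) and r of about 0.46 for the change correlation (n about 35).
3. State, there or under Data analysis, that a non-significant post-treatment difference between BED participants and controls will not by itself be read as normalisation, and that the difference will be reported with its confidence interval.

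The hypotheses need not be relabelled as exploratory. The cost is one reworded paragraph, one added sentence on interpretation, and a stated power that looks less favourable. It needs no further participants or assessments.
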